### Study design and methods

The BRAIN-CT trial is a single-center prospective, randomized, open-label, blinded endpoint study conducted in the ED of Grady Memorial Hospital, a level I trauma center. After completion of initial screening, 350 adults aged 18–85 years will be randomized 1:1 to either a biomarker-published arm (real-time GFAP and UCH-L1 values released to clinicians coupled to education on biomarker data) or a biomarker-blinded arm (standard care without biomarker disclosure). The study flow chart is provided in Figure 1. Allocation uses computer-generated permuted blocks stratified by age (3 Strata: 18–30, 31–50, 51–85 years), biological sex, race (2 Strata: Black, Not Black), Glascow Coma Scale (GCS) (2 Strata: 15, 13–14) and baseline Canadian CT Head Rule risk category (3 Strata: High Risk, Medium Risk, None) to balance key factors in routine decision making. The maximum sample size remains 350 participants for the initially planned cohort. Outcome adjudicators are masked to treatment assignments. Given the pre-existing FDA-approval of the use of the TBI biomarker testing in mild-TBI, the study is deemed no more than minimal risk to participants and a data safety and monitoring board was not required. This study is registered with clinicaltrials.gov (Identifier: NCT06932588), and the study was approved by the Institutional Review Board at Emory University and the Research Oversight Committee at Grady Memorial Hospital.

**Figure 1 fig1:**
[figure not shown]
Study algorithm for enrollment, testing and reporting.

### Inclusion and exclusion criteria

The study inclusion criteria include adults aged 18–85 years old presenting with mild TBI, defined as Glasgow Coma Scale (GCS) score 13–15, within 24 h of injury and without prior head imaging for the same incident.

For definition of timing of injury, this data will be obtained from emergency medical personnel reports, witness reports, reported history from family members or companions, and information from outside facility records if the patient was transferred. If no specific time of injury was determined, the last known normal time will be used. If the last known normal time was within 24 h of presentation, the subject will be included. If the last known normal time is over 24 h, and the exact time of incidence is not available, the patient will not be included.

Key exclusion criteria include:

Subjects with penetrating head injury.History of known brain abnormality including tumor, cerebrovascular malformation, recent brain surgery (within 6 months), prior head injury (within 6 months).Need for emergent surgical intervention for brain or alternate body organ injury.Need for emergent bedside procedures for hemodynamic or orthopedic stabilization.Patients deemed high risk for decline by the provider prohibiting the 15 min delay in obtaining imaging needed for biomarker testing.Minors, pregnant women and prisoners.

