**Methods and analysis:**

This randomized controlled trial will enroll 350 adult patients aged 18–85 years presenting with suspected mild head injury (Glasgow Coma Scale 13–15) within 24 h of trauma. Participants will be randomized into two arms: (1) a biomarker-published group where ED providers receive real-time results of the i-STAT® TBI Cartridge test (detecting GFAP and UCH-L1), and (2) a biomarker-blinded group where results are withheld. The primary outcome is the proportion of patients undergoing CT imaging. Secondary outcomes include hospital length of stay, cost, neurological outcomes, and biomarker correlation with imaging findings. Analysis will involve chi-squared testing, logistic regression, and predictive modeling.

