### Rationale for early biomarker use

GFAP and UCH-L1 enter the bloodstream minutes to hours after mild traumatic brain injury and, when measured on the handheld i-STAT TBI cartridge, yield quantitative results in ≈ 15 min. Large prospective cohorts and FDA-clearance data show that the combined assay has ≥96% sensitivity and >99% NPV for predicting CT-positive intracranial injury within 24 h of trauma, permitting safe imaging deferral in biomarker non-elevated cases (12, 19, 24). Because standard decision rules (e.g., the Canadian CT Head Rule, institutional common practices) still lead to CT scanning in up to 70% of emergency-department patients, embedding real-time GFAP and UCH-L1 testing into the initial evaluation offers an evidence-based, objective tool to reduce unnecessary radiation, crowding, and cost while maintaining diagnostic safety (25).

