### Expected impact of the proposed trial

We are currently unaware of Level I, evidence-based protocols that use blood biomarkers to guide cranial imaging after mTBI. The BRAIN-CT trial is designed to test whether a point-of-care GFAP and UCH-L1 assay, performed within 24 h of injury, can safely reduce CT utilization while maintaining clinical safety and lowering healthcare costs. Previous efforts to limit unnecessary imaging–such as the Canadian CT Head Rule–have demonstrated high sensitivity for detecting clinically significant injuries (2, 6), yet their clinical adoption has been inconsistent. Factors contributing to this include workflow variability, clinician preference, and perceived medico-legal risk (7). The BRAIN-CT trial addresses these limitations by offering an objective, rapid biochemical assessment that is integrated into routine ED workflows. Coupled with rigorous trial methodology, including randomization, blinded outcome adjudication, and cost-effectiveness analysis, BRAIN-CT is positioned to provide critical randomized data on the feasibility, safety, and clinical impact of biomarker-guided imaging decisions, helping to inform future multicenter studies and guideline development.

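### The 24 h entry window ends at presentation, but the assay is described as performed within 24 h of injury, so patients arriving close to 24 h can be sampled outside the stated window

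*Protocol article*

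**What the plan says.** **Entry.** The Protocol article's abstract enrols adults "presenting with suspected mild head injury (Glasgow Coma Scale 13–15) within 24 h of trauma". Under Inclusion and exclusion criteria, the main criterion is presentation "within 24 h of injury and without prior head imaging for the same incident". For an unknown injury time the same section adds "If no specific time of injury was determined, the last known normal time will be used", and then "If the last known normal time was within 24 h of presentation, the subject will be included". That last sentence names presentation outright as the end of the clock.

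**Assay.** Expected impact of the proposed trial says that the trial tests "a point-of-care GFAP and UCH-L1 assay, performed within 24 h of injury". Rationale for early biomarker use bases safe deferral of imaging on at least 96% "sensitivity and >99% NPV for predicting CT-positive intracranial injury within 24 h of trauma".

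**Order of events.** Under Pre-randomization procedures, dashboard screening, detailed eligibility review, written consent (from the patient or a representative), collection of the randomisation variables and randomisation follow one another. Procedures for blinded biomarker arm places the venous draw after these steps. The text shown gives no maximum time to the draw, from either injury or presentation.

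**The concern.** Eligibility and testing run on two different 24 h clocks, and nothing in the text shown reconciles them. A patient can satisfy the entry rule and then give a sample later than the window in which the trial says it tests the assay.

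Two uses of the result are touched. In the published arm, the provider receives it with fixed cut-offs (65 pg/mL for GFAP, 360 pg/mL for UCH-L1) and a refresher on predictive values, whatever the sampling time. A non-elevated result is the one that may support withholding a CT. In the full cohort, the result enters the diagnostic-accuracy objective of Table 2. The text after that table says the validation objectives aim to replicate published data. Replication is cleaner if the samples come from the window for which the article states the performance.

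**Working it through.** The plan gives no figure on this point, so there is none to reproduce. The check compares the clocks and then works out the elapsed time.

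**1. The clocks side by side**

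| Place in the Protocol article | Clock starts | Clock ends |
|---|---|---|
| Abstract | trauma | presentation |
| Inclusion and exclusion criteria, main criterion | injury | presentation |
| Same section, injury time unknown | last known normal | presentation (explicit) |
| Expected impact of the proposed trial | injury | assay performed |
| Rationale for early biomarker use | trauma | not specified |

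The direct mismatch is between the first three rows and the fourth.

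**2. When a patient falls between the clocks**

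Let P be the time from injury to presentation and L the lag from presentation to draw. The time from injury to draw is P + L. The patient is eligible if P ≤ 24 h and sampled in the window if P + L ≤ 24 h. So the affected patients are those with 24 − L < P ≤ 24.

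- P = 24 h: eligible, and necessarily sampled late.
- P = 23.5 h: eligible, and sampled late only if L exceeds 0.5 h.
- The article does not state L. Its figure of about 15 min is the wait for a result, not the time to the draw.

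**3. How many**

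The article gives neither the arrival distribution nor L, so every input here except the 350 is an assumption. Suppose a share s of patients presents 20–24 h after injury, evenly over those 4 hours. The share sampled late is then s × L/4.

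| s | L | Share late | Of 350 |
|---|---|---|---|
| 5% | 0.25 h | 0.05 × 0.25/4 = 0.31% | about 1 |
| 10% | 0.5 h | 0.10 × 0.5/4 = 1.25% | about 4 |
| 5% | 1 h | 0.05 × 1/4 = 1.25% | about 4 |
| 10% | 3 h | 0.10 × 3/4 = 7.5% | about 26 |

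With 1:1 allocation, about half of these would be in the published arm.

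A cruder alternative spreads arrivals evenly over the whole 0–24 h, giving a share of L/24. For L = 0.25, 0.5, 1, 2 and 4 h this is 1.0%, 2.1%, 4.2%, 8.3% and 16.7%, or about 4, 7, 15, 29 and 58 of 350. If most patients arrive early, as one might expect, the counts are lower.

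**4. The primary comparison**

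The endpoint is the proportion with a head CT by randomised arm. Late sampling can occur in either arm and does not depend on allocation, so it does not bias that contrast. Moving the clock to the draw changes neither the stated sample size nor the power calculation.

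**The case against.** The strongest reply is that this is a small wording mismatch with no shown harm. Several parts of it stand.

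- **Validity after 24 h.** A reader might infer that the assay is justified only up to 24 h and gives false negatives beyond it. The document does not support that. The Introduction says both markers stay elevated for at least 24 h, which is a floor. Table 1 includes a cohort with AUCs over 7 days (0.80 to 0.97 for GFAP, 0.31 to 0.77 for UCH-L1). A test counts as non-elevated only when both markers are below cut-off, so GFAP alone can keep it elevated. On the other side, AUCs are not predictive values at this trial's cut-offs, so they do not carry the stated NPV past 24 h either.
- **Who is affected.** A reader might infer that late presenters in general are tested outside the window. The text only permits it, and only for arrivals within L of 24 h. Real-time dashboard tracking and the request to hold CT suggest that the lag is meant to be short.
- **The fallback rule is conservative.** Last known normal precedes the injury, so it overstates elapsed time, and some patients who enter that way will truly be sampled within 24 h. The main criterion and the abstract carry the mismatch more cleanly.
- **Loose comparison text.** The sentence on when the assay is performed is Discussion prose, and the accuracy sentence does not say where its clock ends. Figure 1 and the full protocol are not shown and may set a draw time.
- **Limited consequence.** The CT decision stays with provider and patient, and delayed diagnoses are compared between arms.

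The reply does not remove the mismatch. The article states an eligibility rule whose endpoint differs from its own description of the test.

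**Conclusion.** The point holds as a minor inconsistency with a cheap remedy. The entry rule allows samples to be drawn after the 24 h in which the article says the assay is performed. Those results are used like any other, both by providers in the published arm and in the accuracy analyses.

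Confidence in the mismatch is high and in its size low. The range of about 1–4 of 350 (lag 0.25–0.5 h) to 4–26 (lag 1–3 h) rests on an assumed 5–10% of patients arriving evenly over 20–24 h and on assumed lags. It shows the order of magnitude and is not an estimate. The conclusion extends neither to loss of assay performance just past 24 h nor to bias in the primary CT-rate comparison.

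**What to change.** Reconcile the abstract, Inclusion and exclusion criteria, Rationale for early biomarker use, and Expected impact of the proposed trial, so that one 24 h clock applies throughout. Specifically:

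1. At randomisation, check that the expected initial biomarker draw falls within 24 h of injury, or of last known normal when the injury time is unknown. The REDCap randomisation form can do this from recorded times.
2. Use the recorded draw time to limit the main diagnostic-accuracy analysis to samples drawn within 24 h, and report all samples as a sensitivity analysis.
3. Keep every randomised patient in the primary analysis, including any whose draw slips past 24 h.

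The cost is one sentence in the criteria and one automatic check. A few very late presenters become ineligible, including some with unknown injury time who were in truth within 24 h, because last known normal overstates their elapsed time. If Figure 1 or the full protocol already sets a draw limit, stating it in the criteria closes the eligibility part of the point.

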### Pre-randomization procedures

Screening of eligible patients will be performed by study personnel via real-time tracking of ED dashboard for new admissions or transfers. Triage notes and evaluations will be reviewed for primary eligibility based on age, type of injury, reported GCS, timing of injury and whether existing head imaging is present. If subjects pass screening, they will be approached for review of detailed inclusion and exclusion criteria and for consent process. Written informed consent (from the patient or legally authorized representative) is obtained before any study-specific activities. Providers are notified about patient enrollment and requested to hold off on obtaining CT head imaging until randomization and biomarker data is available. Randomization variables will then be obtained, and subjects will be randomized using an automated algorithm implemented in RedCap into published or blinded biomarker groups.

### Procedures for blinded biomarker arm

For the blinded arm, no further changes are requested from the provider, and a venous blood sample is then collected for point-of-care GFAP and UCH-L1 measurement using the i-STAT TBI cartridge; results are withheld from clinicians. The patient will then be followed up during the hospitalization for reviewing provider decisions, imaging data, clinical outcomes, and disposition as listed in the outcome section.

### Procedures for the published biomarker arm

For the published arm, providers are requested to pause imaging orders until biomarker data is available which requires around 15 min delay. When biomarker data is available, these are printed and provided timely to the provider along with the cut-off for an elevated test. The cut-off used are 65 pg./mL for GFAP and 360 pg./mL for UCH-L1. The provider will also be handed a refresher education on the published data on the negative predictive value (NPV) and positive predictive value (PPV) of the test. The decision whether to pursue a CT of the head will be left to the provider and patient discussion considering the biomarker data. A test is considered non-elevated only if both biomarkers were below the pre-defined cut-off.

### Biomarker testing

Venous blood will be collected by licensed phlebotomists and will be immediately loaded on the iSTAT cartridges as per manufacturer’s instructions. Analysis will be performed as provided by the manufacturer and by dedicated technicians who have been trained and approved by the manufacturer to perform the test. A training log is maintained with the study document for all training sessions and refreshers provided. For every batch/lot of cartridges, independent control testing using manufacturer’s provided controls is performed for quality control.

### Post-randomization in-hospital assessment

After allocation, participants are followed throughout their ED stay and – if admitted– for the duration of hospitalization. Study coordinators prospectively capture whether a head-CT is performed, its timing and radiology results; emergency-department and inpatient length of stay; any neurological deterioration or other adverse events; and final disposition or admission status.

### Post-discharge follow-up

Study staff will conduct structured telephone interviews at 6 months and 12 months after the ED visit to ascertain persistent or late-presenting neurologic symptoms, unplanned healthcare utilization (ED visits, hospital readmissions, outpatient imaging), and any delayed diagnoses of intracranial injury. Future contact is approved by subjects at the time of consent. When participants cannot be reached after three call attempts, electronic health-record review and contact of designated surrogates are attempted to complete the data set. Designated surrogates are individuals determined by the subject to be their emergency contact for the study for future contact and are named at the time of informed consent.

### Primary efficacy analysis

The primary endpoint is the proportion of patients undergoing a head CT scan which will be reported as percentage of total patients. The key hypothesis:

H_0_ (null): There is no difference in CT head scan rates between the published biomarker and blinded biomarker arms.H_1_ (alternative): The published biomarker arm has a significantly lower CT scan rate compared to the blinded biomarker arm.

To evaluate the hypothesis, we will perform univariate analysis using a Pearson’s chi-square test followed by a pre-specified logistic regression model that adjusts for stratification/randomization variables (e.g., site, age, GCS score category), providing an adjusted odds ratio (aOR) and 95% confidence interval (CI). A statistically significant result will be defined with a two-tailed *p*-value of less than 0.05, or adjusted odds ratios for predicting CT head acquisition with a 95% confidence interval below 1.0. In the event the *p*-value approaches the significance threshold (e.g., p between 0.05 and 0.10), results will be interpreted with caution, and effect size estimates will be emphasized to assess the practical impact of the observed differences.

For subgroup analysis across randomization strata, we will use the same testing as primary hypothesis. Then, we will formally test for heterogeneity of treatment effect using interaction terms in the logistic regression models. A *p* < 0.05 for the interaction will be considered evidence of differential efficacy across subgroups (given the exploratory nature of interaction testing).

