## Methods and analysis

### Study objective

The BRAIN-CT trial investigates whether providing emergency-department clinicians with rapid GFAP and UCH-L1 results, via the point-of-care i-STAT TBI cartridge, changes imaging behavior in adults with mild traumatic brain injury. The primary objective (Table 2) is to compare the proportion of patients who receive a head CT scan between a biomarker-published arm and a standard-care (biomarker-blinded) arm; we hypothesize that real-time access to GFAP and UCH-L1 levels will lower the CT scan rate compared with standard management. To address this objective, we have designed a prospective, randomized, open-label, blinded-endpoint (PROBE) adaptive trial that will enroll 350 participants, randomized 1:1 to biomarker-published versus biomarker-blinded arms using permuted blocks stratified by age group, biological sex, race, and baseline Canadian CT Head Rule risk category (Supplementary Table 1). Frequent interim analyses with prespecified efficacy and futility boundaries will permit early stopping if criteria are met.

**Table 2 tab2:** Primary and secondary objectives of the BRAIN-CT trial.

Objective	Category	Objective description	Outcome measured
Primary	–	Evaluate whether real-time access to point-of-care TBI biomarker results (GFAP, UCH-L1) reduces the use of cranial CT imaging.	Proportion of patients undergoing head CT.
Secondary (clinical impact) two-arm comparisons	Clinical decision-making	Assess the impact of biomarker result access on physician decision-making for CT use.	CT imaging timing and provider rationale.
	Efficiency and cost	Determine whether biomarker use reduces ED/hospital length of stay and healthcare costs.	LOS, resource use, hospital charges. Perform a formal ICEA of biomarker testing versus standard care.
	Patient outcomes	Compare short-term outcomes between arms (neurological deterioration, readmissions, GOS, GCS).	GOS-E/GCS at 6 months and 1-year follow-up, neurological symptoms.
	Radiation exposure	Quantify radiation dose reduction per patient between arms.	Directly measure a key safety benefit.
	Disparity analysis	Identify patient subgroups (e.g., by age, injury mechanism, comorbidity) where biomarkers influence decision-making.	Stratified CT usage, subgroup analysis of impact.
	Safety monitoring	Monitor for adverse outcomes from missed injuries in biomarker-guided arm.	Adverse events, unexpected deterioration, delayed diagnoses.

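### Subgroup analyses reuse the primary significance rule, and any interaction p<0.05 counts as evidence, giving roughly a one-in-five to one-in-four chance of a false claim that the effect differs

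*Protocol article*

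**What the plan says.** The Protocol article, Primary efficacy analysis, sets a two-sided primary criterion for the p-value or the odds ratio: "value of less than 0.05, or adjusted odds ratios for predicting CT head acquisition with a 95% confidence interval below 1.0". The methods are a Pearson chi-square test followed by an adjusted logistic regression.

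The next paragraph carries this into subgroups: "For subgroup analysis across randomization strata, we will use the same testing as primary hypothesis". It continues: "Then, we will formally test for heterogeneity of treatment effect using interaction terms in the logistic regression models". An interaction p-value below 0.05 "for the interaction will be considered evidence of differential efficacy across subgroups (given the exploratory nature of interaction testing").

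Study design and methods lists the stratification factors: age (3 levels), sex, race (2), GCS (2) and "baseline Canadian CT Head Rule risk category (3 Strata: High Risk, Medium Risk, None) to balance key factors in routine decision making". The design paragraph under Study objective lists four factors and leaves out GCS.

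Table 2 has a secondary objective on subgroups: "Identify patient subgroups (e.g., by age, injury mechanism, comorbidity) where biomarkers influence decision-making".

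**The concern.** Three features of the stated rule matter together.

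- The significance criterion of the whole trial is applied within strata that hold only part of the sample. Whether one level reaches p<0.05 then depends heavily on its size. It says little about whether the effect differs from that in another level.
- These within-stratum tests carry no exploratory label, and nothing makes them depend on the interaction result. The exploratory remark attaches to interaction testing only.
- The interaction tests are called exploratory, yet one p<0.05 among several is to be read as evidence of differential efficacy. The label and the conclusion do not match.

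At stake is what the trial may say about who benefits. Race and sex are among the stratification factors, so a false statement that disclosure changes CT use in one group and not another is possible under the rule as written. The primary conclusion is not at stake.

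**Working it through.** **Inputs**
- From Sample size justification: 300 evaluable patients (150 per arm), 70% baseline CT use and a 15% reduction, taken here as 70% vs 55%.
- From Primary efficacy analysis: two-sided 0.05 for each test.
- From Study design and methods: 3 + 2 + 2 + 2 + 3 = 12 levels in 5 factors, with sex taken as two levels. Without GCS this is 10 levels in 4 factors.
- Assumed: subgroup sizes, independence between factors, and the same baseline CT rate in every level. The article gives none of these.

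**The plan's own figure.** The article states no error rate for subgroups. Its only related figure is at least 80% power with 150 per arm. The pooled two-proportion formula used below gives 76.8% for 70% vs 55%. That gap is a separate matter and does not affect this point.

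**Independence arithmetic, no true effect.** The chance of at least one false positive among k tests is 1 − 0.95^k.
- Five interactions: 1 − 0.95^5 = 22.6%. Four interactions: 1 − 0.95^4 = 18.5%.
- Twelve level tests: 1 − 0.95^12 = 46.0%. This is too high, because the levels of different factors share patients.

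**Simulation, to allow for the overlap.** Two separate simulations used N = 300 and 1:1 allocation, with a chi-square test in each level. One ran 4,000 trials per scenario with a heterogeneity test per factor. The other ran 3,000 with a likelihood-ratio interaction test per factor in the adjusted logistic model. Each used an equal and an unequal set of subgroup sizes. The second simulation's unequal set went down to 15% in the smallest level.

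| Event | First simulation (equal / unequal) | Second simulation (equal / unequal) |
|---|---|---|
| No effect: any of 12 level tests p<0.05 | 34.8% / 35.8% | 35.5% / 35.2% |
| No effect: any level test p<0.05 in the favourable direction | not computed | 17.9% / 18.0% |
| No effect: any of 5 interactions p<0.05 | 21.6% / 18.9% | 26.7% / 24.7% |
| No effect: either kind | not computed | 43.8% / 41.7% |
| Uniform 70% vs 55%: any interaction p<0.05 | 22% / 21% | 25.7% / 25.4% |

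The interaction rates differ because the two simulations used different tests. Both lie around the 22.6% expected under independence.

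**Power inside a level, 70% vs 55%.** Power = Φ{[0.15 − 1.96·√(2 × 0.625 × 0.375/n)] / √[(0.70 × 0.30 + 0.55 × 0.45)/n]}.
- n = 50 per arm (one third of the sample): (0.15 − 0.1898)/0.0957 = −0.416, so 33.9%.
- n = 75 per arm (one half): (0.15 − 0.1549)/0.0781 = −0.063, so 47.5%.

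**What this does to level p-values when the effect is identical everywhere.** The levels of one factor do not overlap, so their tests can be treated as independent.
- Two equal levels: the verdicts disagree with probability 2 × 0.475 × 0.525 = 50%.
- Three equal levels: 1 − 0.339³ − 0.661³ = 67%.

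A significant level next to a non-significant one is therefore a common result of a uniform effect.

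**The case against.** The strongest reply is that the plan ties differential efficacy to the interaction test alone. It never says that significance in one level and not in another shows a difference, and a formal interaction test is the accepted guard against that fallacy. This stands. With a uniform effect, about 90–91% of simulated trials have some factor with one level significant and another not. A reader might infer that the plan would declare a spurious subgroup difference that often. The text does not support this: under its own rule the false-claim rate is the 21–26% for interactions.

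Other points on that side:
- **Order.** A reader might object that the level tests come before the interaction tests. The sequence is not a gate, and reversing it changes no error rate.
- **Number of tests.** Twelve levels is an inference. The article gives no count, and Study objective omits GCS. Fully crossed strata would be 3 × 2 × 2 × 2 × 3 = 72 cells, about four patients each, so testing factor by factor is the workable reading. With four factors the interaction figure is 18.5%.
- **Same testing.** The phrase could mean the same methods without a claim of significance. But the significance criterion stands in the paragraph just before, and no other is given for subgroups.
- **Table 2.** A reader might take the subgroup objective to name race and sex. It does not. They enter only as stratification factors.
- **Exploratory label and unseen SAP.** The label softens the problem for interactions but not for the level tests. A missing multiplicity adjustment could properly sit in the SAP and is not the point here. The point is the rule that the article does state.

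**Conclusion.** The point holds as a defect in a stated rule, limited to subgroup conclusions. The primary criterion is applied within strata without qualification, and an interaction p<0.05 is given more weight than its exploratory label allows.

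With no true effect, a false interaction appears in about 19–27% of trials over five factors, and a false level result in about 35%, of which about half are in the favourable direction. With a uniform effect, false interactions remain at about 21–26%. It would go too far to call a spurious finding likely under no effect, since even the combined rate of 42–44% is below one half.

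The level p-values do not inform heterogeneity, because they mainly reflect power of about 34–48% per level. The plan does not formally base its heterogeneity claim on them.

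The simulated figures rest on assumed subgroup sizes, independent factors and equal baseline CT rates. They use the chi-square criterion only, and the alternative confidence-interval criterion could raise the level-test rates slightly. The primary analysis and its error rate are untouched.

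**What to change.** In Primary efficacy analysis:
1. Replace the within-stratum significance tests with the difference in CT proportion in each level and its 95% confidence interval, without a p-value or significance statement.
2. Base any statement on heterogeneity on one interaction test per stratification factor, and state how many such tests were done.
3. Describe an interaction p<0.05 as hypothesis-generating instead of as evidence that efficacy differs.

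Apply the same rule to the Table 2 subgroups, and make the list of stratification factors agree between Study objective and Study design and methods so that the count is fixed.

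Multiplicity adjustment is optional and is needed only if a confirmatory claim is wanted. Holm's method would serve. As a guide, five tests at 0.05/5 = 0.01 bring the family-wise error to 1 − 0.99^5 = 4.9%, with less power to detect a real difference.

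The cost is wording only. The trial gives up stand-alone claims of significance in a subgroup. Sample size, conduct and the primary analysis do not change.
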